## Abstract

**Background:**

Generalized anxiety disorder (GAD) is a psychiatric disorder characterized by a constant and unspecific anxiety that interferes with daily-life activities. Its high prevalence in general population and the severe limitations it causes, point out the necessity to find new efficient strategies to treat it. Together with the cognitive-behavioural treatments, relaxation represents a useful approach for the treatment of GAD, but it has the limitation that it is hard to be learned. To overcome this limitation we propose the use of virtual reality (VR) to facilitate the relaxation process by visually presenting key relaxing images to the subjects. The visual presentation of a virtual calm scenario can facilitate patients' practice and mastery of relaxation, making the experience more vivid and real than the one that most subjects can create using their own imagination and memory, and triggering a broad empowerment process within the experience induced by a high sense of presence.

According to these premises, the aim of the present study is to investigate the advantages of using a VR-based relaxation protocol in reducing anxiety in patients affected by GAD.

**Methods/Design:**

The trial is based on a randomized controlled study, including three groups of 25 patients each (for a total of 75 patients): (1) the VR group, (2) the non-VR group and (3) the waiting list (WL) group. Patients in the VR group will be taught to relax using a VR relaxing environment and audio-visual mobile narratives; patients in the non-VR group will be taught to relax using the same relaxing narratives proposed to the VR group, but without the VR support, and patients in the WL group will not receive any kind of relaxation training. Psychometric and psychophysiological outcomes will serve as quantitative dependent variables, while subjective reports of participants will be used as qualitative dependent variables.

**Conclusion:**

We argue that the use of VR for relaxation represents a promising approach in the treatment of GAD since it enhances the quality of the relaxing experience through the elicitation of the sense of presence. This controlled trial will be able to evaluate the effects of the use of VR in relaxation while preserving the benefits of randomization to reduce bias.

**Trial Registration:**

NCT00602212 (ClinicalTrials.gov)

## Background

According to the DSM-IV-TR [1] the essential features of generalized anxiety disorder (GAD) are an excessive anxiety and an uncontrollable worry (apprehensive expectation), occurring more days than not for a period of at least 6 months, about a number of events or activities. Anxiety and worry are often accompanied by additional symptoms like restlessness, being easily fatigued, difficulty concentrating, irritability, muscle tension, and disturbed sleep. Although individuals with GAD may not always identify their worries as "excessive," they report subjective distress due to constant worry, have difficulty in controlling it, or experience related impairment in social, occupational, or other important areas of functioning. During the course of the disorder, the focus of worry may shift from one concern to another. Intensity, duration, or frequency of anxiety and worry are far out of proportion to the actual likelihood or impact of the feared event. Differently from other anxiety disorders usually associated to specific stimuli or situations, GAD is characterized by a constant and unspecific anxiety, involving a process of interacting systems (attentional, conceptual, imaginal, physiological, affective, and behavioural) that unfold over time in continual response to a constantly changing environment.

A quite recent study affirms that the prevalence of GAD in the general population might actually be as high as 5 to 8% [2], while among individuals seeing their physicians for psychological problems the 25% of them have a diagnosis of pure GAD. Indeed, in primary care facilities, GAD is the most frequent anxiety disorder and the second most frequent of all mental disorders [3,4]. GAD is more prevalent in women and much more prevalent in youths, where 12% to 20% are affected [5-7]. The age of onset is between the late teens and early twenties and the average duration is about 20 years, suggesting a chronic and fluctuating course that often worsens during time of stress. People with general nervousness, depression, inability to tolerate frustration, and feelings of being inhibited are more likely to be shown in GAD patients. People with GAD tend to have more conflicts with others, are very hard on themselves, and tend to avoid common situations for fear of worry and anxiety. In youths, GAD often leads to lower levels of social supports, academic underachievement, underemployment, substance use and high probability of developing other psychiatric disorders. In epidemiological studies of GAD a consistent finding has been that over 90% of individuals who meet criteria for GAD in a given year will also have at least one other DSM-IV diagnosis [8].

The high prevalence of GAD in the general population and the severe limitation it causes, point out the necessity to find new strategies to treat it in a more efficient way. GAD is usually treated with medications and/or psychotherapy. In particular, the two most promising treatments seem to be cognitive therapy and applied relaxation. As shown by numerous studies, both of these treatments are equally effective [9,10] immediately and over long-term periods. Cognitive treatment helps patients to recognize and alter patterns of distorted thinking and dysfunctional behaviour, while relaxation serves to reduce the increased physical arousal often strictly associated to this disorder. In fact, physical arousal can be voluntarily altered with training in relaxation skills that enables patients to shift physical functions voluntarily toward those that naturally occur in a relaxed state [11]. Progressive muscle relaxation and more general imagery techniques can be used as therapy progresses since the ability to relax, and to do it in any place or situation, is vital to reduce the anxiety level.

Even if relaxation represents a useful approach for the treatment of GAD, it presents an important limitation: it is difficult to be learned. Traditionally, relaxation techniques are verbally taught by a therapist or recorded on an audiotape, while recently a series of CDs of calming music have been used to help individuals to relax themselves, showing positive effects on anxiety reduction by achieving psychological benefits including distraction and sense of control over symptoms. Music interventions also have reported good results to reduce state and trait anxiety, to ease stress, and to increase relaxation [12-14]. These CDs strengthened the positive effect of calm and sedative music with relaxation techniques to achieve enhanced effects. To increase effectiveness, commercial relaxation DVDs have also integrated visual stimuli. In such a delivery, the visual representation of the scenario supports the process of relaxation creating an isolated context in which the subject can feel to stay.

Virtual reality (VR) can also be used to facilitate relaxation processes in stressed or anxious subjects [15] by visually presenting key relaxing images [16]. The advantage of VR compared to CDs or DVDs is its ability to induce a sense of presence in the users, that is defined as the "feeling of being in a world that exists outside of the self " [17]. The visual presentation of a virtual calm scenario can facilitate patients' practice and mastery of relaxation, making the experience more vivid and real than the one that most subjects can create using their own imagination and memory, and triggering a broad empowerment process within the experience induced by a high sense of presence. VR can be provided using desktops or laptops connected to a variety of peripheral devices, such as head-mounted displays and joysticks and even trough different kinds of mobile devices, such as the new generation of portable audio-visual devices, cellular phones and hand-held personal digital assistants (PDAs) equipped with enough raw horse power to deliver a good 3D experience.

### Aim of the study

Knowing that relaxation techniques are as effective as cognitive and behavioural methods in the treatment of GAD and considering the critical point regarding the difficult in learning them, the aim of the present study is to investigate the advantages of using a VR-based relaxation protocol in reducing anxiety in patients affected by GAD. The following hypothesis will be tested:

I) GAD patients exposed to a VR relaxing environment learn how to relax themselves easier and more efficiently than patients exposed to a traditional relaxation protocol;

II) There is a positive correlation between the treatment efficacy and the sense of presence experienced by the patients during the treatment sessions.

3-D audio-visual experiences, whose critical aspect is to induce a feeling of presence and engagement, will be presented to the subjects in order to help them to become relaxed. Through the link between the feeling of presence and the emotional state, VR relaxing environments will be used to reduce the anxiety levels in their users [15].

## Methods

The present trial is based on a randomized controlled study, including three groups of patients: (1) the VR group, (2) the non-VR group and (3) the waiting list (WL) group. Patients diagnosed with GAD according to the DSM-IV criteria, will be randomly assigned to one of these three groups.

### Subjects

Patients will be recruited in a public health-care structure in Milan, Italy, according to the diagnosis received from their treating responsible psychiatrist or psychologist. In order to be included in the study, patients have to meet the following criteria: (1) primary diagnosis of GAD; (2) requesting treatment for their GAD; (3) older than 17 and younger than 70; (4) no depressive disorder preceding the current episode of GAD or requiring immediate treatment; (5) no behaviour therapy received for their GAD; (6) no evidence of organic mental disorders accounting for the complaints, mental retardation, psychotic disorders, alcohol or drug dependence; (7) no migraine, headache, seizure disorder, and vestibular abnormalities since they represent significant contraindications for the use of VR.

A power analysis was conducted in order to evaluate the number of patients needed to detect a significant difference (Effect size f ≥ 0,40) between the three groups (VR, non VR and WL) with a power of 0,90. The analysis showed a necessary total sample size of 75, 25 in each group, with α = 0,5, two-tailed. Both males and females will be included. All participants have to be clinically stable, meaning no change in dose of psychotropic medications 1 month before inclusion. Since over 90% of individuals who meet criteria for GAD in a given year will also have at least one other DSM-IV diagnosis [8], patients will be included in the study even if they present at least one more psychiatric diagnosis.

Before participating in the study, each patient will be provided with written information about the study and invited to give written consent for inclusion. The present research is in compliance with the Helsinki Declaration.

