### Psychometric assessment

The following psychometric questionnaires will be administered to each patient at pre-treatment, upon completion of the clinical trial, and after 6-month and 12-month follow-up periods:

- PSWQ – Penn State Worry Questionnaire – [18]. The PSWQ is the only existing questionnaire specific for GAD with an extensive validation on Italian population. It analyzes symptoms of pathological worries that characterize this disorder.

- BAI – Beck Anxiety Inventory – [19]. The BAI is a standardised and well-used assessment measure with good psychometric properties used to assess anxiety. It is a 21-item scale which covers cognitive, behavioural and physiological symptoms of anxiety.

- Anti – Anxious Thoughts Inventory – [20]. The AnTI included 22 items that investigate 3 different categories of worries: social worries, worries linked to health and the metacognitions about worry (fear of fear). The available data show that the AnTI questionnaire is sensitive to treatment effects.

- CID – Anxiety and Depression Scales of the Clinical Interview for Depression – [21]. The CID anxiety scale consists of 4 items rated on a 7-point scale. The CID depression scale includes 10 items.

- STAI – State-Trait Anxiety Inventory – [22]. The STAI measures a person's situational (or state) anxiety, as well as the amount of anxiety a person generally feels most of the time (trait). The two scales contain 20 items each, which may be scored 1 (not at all) to 4 (very much so).

Immediately before and after each treatment session subjects will be also asked to rate their levels of subjective anxiety on the Visual Anxiety Scale (VAS-A). In order to verify if there is a positive correlation between the treatment efficacy and the sense of presence experienced by the patients during the treatment sessions, the Itc-Sense of Presence Inventory (ITC-SOPI) [23] will be administered to each patient exposed to the VR environment after each session. The ITC-SOPI is a questionnaire composed by 44 items, that investigates the sense of presence experienced during the VR exposure.

Moreover, as homework, patients will be asked to fill some forms regarding their relaxing experiences.

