### Experimental design

Patients included in the study will be randomly assigned to one of the following three conditions:

(I) VR: subjects will be taught to relax using VR relaxing environments and audio-visual mobile narratives;

(II) non-VR: patients will be taught to relax using the same relaxing narratives proposed to the VR group, but without the VR support;

(III) WL: patients included in the waiting list group will not receive any kind of relaxation training.

Psychometric and psychophysiological outcomes will serve as quantitative dependent variables, while subjective reports of participants will be used as qualitative dependent variables.

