### Trial analysis

Data will be entered in SPSS. Descriptive methods will be used to demonstrate the consistency of the three groups, describe participant characteristics and report levels of participation and drop out. Analysis of variance will be used to evaluate baseline characteristics of the three groups involved in the study, overall significance of improvement across outcome measures, and drop out versus maintainers. For each patient, change in psychometric and physiological measures will be calculated and analysed using t-test for matched groups for both intervention and control groups. The magnitude of change will be estimated and the 95% confidence intervals given.

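### The stated power is for the three-arm omnibus test, whereas hypothesis I is VR against non-VR, for which no power is given and no between-arm test is named

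*Protocol article*

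**What the plan says.** **Power.** The Subjects section of the protocol article sizes the trial on "Effect size f ≥ 0,40) between the three groups (VR, non VR and WL) with a power of 0,90" and arrives at a "necessary total sample size of 75, 25 in each group, with α = 0,5, two-tailed". No other power or effect-size figure is given.

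**Hypotheses.** Under Aim of the study, hypothesis I is that patients exposed to VR "learn how to relax themselves easier and more efficiently than patients exposed to a traditional relaxation protocol". Hypothesis II is that "There is a positive correlation between the treatment efficacy and the sense of presence experienced by the patients". Neither mentions the waiting list (WL).

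**Comparator.** Under Experimental design, the non-VR "patients will be taught to relax using the same relaxing narratives proposed to the VR group, but without the VR support". That makes the non-VR arm the traditional-relaxation comparator of hypothesis I.

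**Analysis.** The Trial analysis section plans analysis of variance for, among other things, "overall significance of improvement across outcome measures", and matched t-tests on change in the intervention and control groups. It names no between-arm comparison of VR with non-VR.

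**Presence.** Under Psychometric assessment, the presence questionnaire "will be administered to each patient exposed to the VR environment after each session", so hypothesis II draws on the VR arm only.

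**The concern.** The power of an omnibus F test depends on f, the total sample and alpha, not on which arm produces the difference. One of the three arms here is untreated and the other two both receive applied relaxation, which the Background section describes as effective. An f of 0.40 could therefore come wholly from both active arms doing better than WL, with VR adding nothing.

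The plan's power figure and its main hypothesis thus concern different comparisons. Two misreadings become possible. A significant overall F could be taken as support for VR when it reflects treatment against no treatment. A non-significant VR against non-VR comparison could be taken as a negative result from a trial with 90% power, when its power for that comparison may be much lower.

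**Working it through.** **Inputs.** From the Subjects section: f = 0.40, target power 0.90, N = 75, 25 per arm, two-tailed. Alpha is printed as 0,5. I take 0.05 as what was meant; this is an assumption, and results at the printed value are given below.

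**Step 1: the plan's own figure.** For a one-way ANOVA with three groups, the noncentrality is λ = N·f² = 75 × 0.16 = 12, with 2 and 72 degrees of freedom.
- At alpha 0.05 the power is 0.869. Power of 0.90 needs N = 84 (28 per arm).
- At the printed alpha of 0.5 the power is 0.994, and 0.90 would need only N = 30.
- At alpha 0.10 the power is 0.927, and 0.90 would need N = 69.

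None of these gives 75 at 0.90. That and the printed alpha are separate matters. The omnibus power used from here on is 0.87.

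**Step 2: VR minus non-VR when f = 0.40.** Let D be the VR–WL distance in SD units, with non-VR a fraction q of the way from WL to VR. The standard deviation of the three means is D·√(2(1 − q + q²))/3. Setting this to f gives D = 3f/√(2(1 − q + q²)), and the VR minus non-VR difference is d = (1 − q)·D.
- q = 1: D = 1.2/√2 = 0.85, so d = 0.
- q = 1/2: D = 1.2/√1.5 = 0.98, so d = 0.49.
- q = 0: D = 0.85, so d = 0.85.

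**Step 3: power of the two-arm contrast.** Noncentral t with 25 per arm, 48 degrees of freedom, noncentrality d·√(25/2), two-sided alpha 0.05:

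| Pattern of means (all f = 0.40, omnibus power 0.87) | d | Power, VR vs non-VR |
|---|---|---|
| VR = non-VR, WL apart (q = 1) | 0 | 0.05 (the type I error rate) |
| q = 3/4 | 0.24 | 0.13 |
| q = 2/3 | 0.32 | 0.20 |
| Evenly spaced (q = 1/2) | 0.49 | 0.40 |
| non-VR = WL (q = 0) | 0.85 | 0.84 |

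Power of 0.90 would need 89 per arm at 0.49 SD and 31 per arm at 0.85 SD. Using the three-group error term (72 degrees of freedom) barely changes the results: 0.401 for the evenly spaced row and 0.841 for the last.

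A simulation of the first row (40,000 runs) gave omnibus rejection 0.867 and VR against non-VR rejection 0.051.

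**Step 4: what 25 per arm can detect.** Solving the same formula for d gives 0.81 SD at 80% power and 0.94 SD at 90%.

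**Side note on hypothesis II.** By Fisher's z with n = 25, 80% power two-sided needs r = tanh((1.960 + 0.842)/√22) = tanh(0.597) = 0.535, or about 0.54.

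**The case against.** **The article scopes its figure correctly.** A reader might infer that it claims 0,90 for hypothesis I. It does not: the figure is attached to a difference among three groups, which fits the three-arm design and the planned ANOVA, and the Discussion gives WL a role in attributing results. This stands. The mismatch is between the powered comparison and the leading hypothesis, which is a criticism of a design choice and not of a false statement.

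**Contrasts may be specified elsewhere.** A reader might infer that hypothesis I will never be tested. The document does not support that: a full protocol or analysis plan may name the contrast, and its absence from an article would not be a finding alone. The point rests on the figure the article does state.

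**The result depends on alpha.** At the printed 0,5 the evenly spaced contrast would have power 0.86, not 0.40. The numbers do depend on reading alpha as 0.05. The logic does not, because omnibus power ignores which arm differs at any alpha.

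**Favourable patterns exist.** The article's f is a floor, and if non-VR equals WL the contrast has power 0.84. At f = 0.40 it passes 0.90 only if non-VR is worse than WL (at most 0.98 SD, power 0.92). A one-sided test would give 0.53 for evenly spaced means and 0.91 for non-VR = WL, but the article states two-tailed. Baseline adjustment could help, but the stated figure is not based on it.

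**Hypothesis II.** Trials are often not powered for a mechanistic correlation within one arm, and this one is directional: one-sided, the 80% figure falls to about r = 0.49. The lack of power for it is not a defect of equal weight.

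**Conclusion.** The point holds as a mismatch. The only stated power is for the three-arm omnibus test, and it does not describe VR against non-VR. At f = 0.40 the omnibus power is 0.87 throughout, while power for VR minus non-VR runs from 0.05 through 0.40 to 0.84 with non-VR anywhere at or between VR and WL.

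This rests on alpha 0.05 two-sided, equal variances, an unadjusted comparison and all 25 patients per arm analysed. It also rests on reading the calculation as an omnibus one; the article does not use that word, but no other standard reading fits an f across three groups.

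It would go too far to conclude that the trial is underpowered for hypothesis I. The article gives no expected VR minus non-VR difference, so only the range and the detectable difference can be stated. The point should be corrected, but it does not call for a larger trial.

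**What to change.** 1. Name the between-group contrast VR minus non-VR as the test of hypothesis I, and make the contrasts with WL secondary.
2. Restate the power paragraph so that the omnibus figure cannot be read as power for hypothesis I. State that 25 per arm detects 0.81 SD between VR and non-VR with 80% power and 0.94 SD with 90% (two-sided alpha 0.05, unadjusted, no dropout). Confirm the intended alpha at the same time.
3. Keep N at 75.
4. As a side note, report hypothesis II as r with its 95% confidence interval in the 25 VR patients, noting that 80% power needs r of about 0.54 two-sided.

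The cost is rewording one paragraph and fixing the order of the tests. The downside is a less favourable stated power for the question of interest.

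### The sample-size inputs do not give 75 patients: α is printed as 0,5, and at 0.05 the design has power 0.87, not 0.90

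*Protocol article*

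**What the plan says.** The only justification of the sample size is in the Subjects section of the protocol article. The target is a difference with "Effect size f ≥ 0,40) between the three groups (VR, non VR and WL) with a power of 0,90". The result follows: "The analysis showed a necessary total sample size of 75, 25 in each group, with α = 0,5, two-tailed". The Methods/Design part of the abstract gives the same number as the planned enrolment: "three groups of 25 patients each (for a total of 75 patients".

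The power sentence does not name a test. The Trial analysis section does name one for group comparisons: "Analysis of variance will be used to evaluate baseline characteristics of the three groups involved in the study, overall significance of improvement across outcome measures". That section also plans 95% confidence intervals, a report of drop-out, and a comparison of those who drop out with those who stay. It gives no expected drop-out rate. Follow-up runs to 12 months.

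**The concern.** The sentence gives every input to a standard calculation (number of groups, effect size, power, α) together with its result, so it can be checked. Three things look wrong.

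- **The error rate.** α is printed as 0,5. Read literally, that is a 50% chance of a false positive.
- **The power.** If α is read as 0.05, a reader who mentally supplies the missing zero will take the trial to have 90% power. That holds only if 75 is the right answer at 0.05.
- **The tails.** Cohen's f belongs to an F test across groups. The omnibus F test has no two-tailed form, so the phrase does not describe the calculation.

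The number called necessary is also the number to be enrolled, so the power claim has no margin if patients leave. At stake is the type II error: how far a null result from this trial could be trusted.

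**Working it through.** **Inputs**

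| Input | Value | Source |
|---|---|---|
| Groups | k = 3, equal size | Subjects |
| Effect size | f = 0.40, the stated minimum | Subjects |
| Target power | 0.90 | Subjects |
| α | 0.5 as printed; 0.05 as the likely intent | Subjects; 0.05 is our reading |
| Total N | 75 = 3 × 25 | Subjects; abstract |
| Test | one-way analysis of variance | f between three groups; Trial analysis |
| Drop-out | none stated | our assumption where used |

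**Formula.** Under the alternative, the F statistic has a noncentral F distribution with 2 and N − 3 degrees of freedom and noncentrality λ = N·f². Power is the probability that it exceeds the upper-α point of the central F with the same degrees of freedom. At N = 75, λ = 75 × 0.16 = 12.0, with 2 and 72 degrees of freedom.

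**Step 1: α = 0.5 as printed.** The critical value at N = 75 is F = 0.70, and power is 0.994. The smallest equal-group N with power of at least 0.90 is 30 (λ = 4.8, power 0.907). So 75 does not follow.

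**Step 2: α = 0.05.** The critical value at N = 75 is F = 3.12.

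| N | λ | Power |
|---|---|---|
| 75 | 12.00 | 0.869 |
| 78 | 12.48 | 0.883 |
| 81 | 12.96 | 0.895 |
| 84 | 13.44 | 0.907 |

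The smallest equal-group N for 0.90 is 84, or 28 per group. Again 75 does not follow. The type II error is 13%, against a stated 10%.

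**Step 3: other values of α.** At α = 0.10, 69 patients are needed; at α = 0.025, 96. With N = 75 and power 0.90 held fixed, solving for the remaining input gives α = 0.071 at f = 0.40, or f = 0.42 at α = 0.05. The document states neither.

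**Step 4: other methods at α = 0.05.** A large-sample chi-square approximation gives power 0.883 at N = 75 and needs about 80 patients. A pairwise t test with an assumed standardised difference of 0.8 and 25 per group gives 0.79 two-sided and 0.87 one-sided. None of these returns 75 for power 0.90.

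**Step 5: effect of losing patients (α = 0.05, f = 0.40).** The rates are assumptions.

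| Assumed loss | Analysed N | Power |
|---|---|---|
| 0% | 75 | 0.869 |
| 10% | 68 | 0.831 |
| 15% | 64 | 0.805 |
| 20% | 60 | 0.776 |
| 25% | 56 | 0.743 |

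**The case against.** The strongest reply is that the power sentence names no model and that patients are measured repeatedly. A between-groups analysis of variance on two measurements multiplies λ by 2/(1 + ρ), where ρ is the within-patient correlation. With ρ = 0.8, λ at N = 75 is 12 × 2/1.8 = 13.3 and power is 0.903, and 75 is then the smallest equal-group N that reaches 0.90. Likewise, adjusting for baseline divides λ by 1 − r², where r is the correlation with baseline, and brings power at N = 75 to about 0.90 when r is about 0.30. A journal article condenses the full calculation, so an unprinted correlation need not be an error.

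The arithmetic is right, and it shows that 90% power at 75 is attainable under some models. It does not reproduce the printed claim. Both routes need a correlation that the document does not give. The first tests an average over time that includes baseline, which is not a test of improvement. An f between three groups, with analysis of variance as the named method, supports the one-way reading.

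Four other points bear on how serious this is:

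- The α is very likely a lost zero. The planned 95% confidence intervals point to 0.05, and no analysis is planned at 50%. This is accepted.
- The shortfall without loss is small. This is also accepted.
- No time point is attached to the 0.90, so loss over 12 months need not apply to it in full; it may refer to the end of the seven-week treatment. This is fair, and it is why the loss figures are shown as a range.
- The mention of two tails has no numerical effect. True, but it is still wrong.

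**Conclusion.** The concern holds. The printed inputs do not yield 75 at the printed α or at α = 0.05. The printed α overstates the intended error rate tenfold if 0.05 was meant. Once that is corrected, the stated power is still too high: 0.87 instead of 0.90, equivalent to 9 patients too few or to an effect of f = 0.42 instead of 0.40.

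This rests on a one-way analysis of variance on a single measurement per patient, which is the reading the text supports. It does not depend on any drop-out assumption. Loss would widen the gap, to 0.83 at 10%, 0.78 at 20% and 0.74 at 25%, but those rates are ours.

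The error does not invalidate the trial. It needs correcting because this sentence is the document's only basis for the trial's size, and neither the error rate nor the power in it can be taken as printed.

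**What to change.** In the Subjects section:

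1. Print α = 0.05.
2. Delete the reference to two tails and name the test, a one-way analysis of variance F test across the three groups.
3. Restate the claim: 75 analysed patients give power 0.87 for f = 0.40, or 0.90 for f of about 0.42.
4. State an expected drop-out rate and the power it leaves, for example 0.78 if 20% are lost.

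If the original calculation used repeated measurements or baseline adjustment, give that model and its assumed correlation in place of item 2's one-way test and item 3's figures, and recompute item 4 on the same model.

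The enrolment target can stay at 75. The cost is one corrected sentence and a slightly less favourable power figure.
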